### Random allocation

After receiving the consent form, the participant will be randomised into one of the three study arms, with a 1: 1: 1 allocation ratio. Randomisation will be blocked to ensure that groups are of equal size and that groups of six participants for each arm are regularly formed. The blocks will be of variable size (3, 6, 9) to protect the concealment. There is no stratification. The randomisation sequence will be implemented in the REDCap software, so none of the team members will know in advance which arm the next participant will be assigned to.

### Sample size

To assess the effectiveness of each intervention, we will recruit a sample of 30 participants per arm, for a total N of 90 participants randomised into three groups. This sample size appears sufficient to detect a large pre-post effect on body dissatisfaction (primary outcome) according to data reported in previous studies [36], and including a hypothetical dropout rate of 10%. The effect sizes (Cohen’s d) reported in the Stice studies are large for the BP or the HW and generally exceed 0.50 (e.g. ref. [36] where the effect sizes were 0.90). To capture a pre-post effect of 0.50 with a power of 0.80 and a probability of 0.05, a sample of 27 people is needed for an intervention (calculated with G * Power 3.1 [37]).

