### Data management and statistical analysis

Participants will receive a code upon entering the study. Coding will start at 001 and continue with +1. The signed consent form will contain the equivalence between the participant’s contact details and their code. All forms will be printed and stored in a locked drawer. The electronic forms will be stored in a protected space, which will be backed up regularly during the study. At the end of the study, the data will be stored in a repository, which guarantees that archiving and data sharing will be performed in accordance with FAIR principles. The study will be internally monitored.

The questionnaires (validated questionnaires, socio-demographic variables, satisfaction indices) will be implemented in the REDCap software [52], hosted at the HES-SO (University of Applied Sciences and Arts, Western Switzerland), which will be used to collect the data. The participant’s e-mail address will need to be entered in the platform to allow the surveys to be sent, but it will be coded as an identifier and not exported to the database. Only the participant’s code will represent the participant in the final database.

Missing data will be handled with a single imputation method. To test the hypothesis stipulating a pre-post difference between the participants of the two intervention groups and the participants of the control list, analyses of variance (ANCOVA analyses of covariance with time pre in covariate) will be conducted in order to compare the three groups BP, HW, and waiting list on the different dependent variables, with post-hoc analyses to compare the groups two by two. The primary outcome is body dissatisfaction assessed with the BSQ-8C. Similar analyses will be carried out for the secondary outcomes. Regarding the stability of the intervention and the hypothesis predicting that the observed effects will be maintained after one month of follow-up, repeated measures analyses of variance will be performed. The statistical analyses will be carried out with completers and intent-to-treat.

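### The 27 participants per intervention match a one-sided paired test that the protocol does not declare; on a two-sided 5% pre-post test, 27 completers give power of about 0.71, not 0.80

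*Protocol article*

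**What the plan says.** The Sample size section gives the target effect, the power, the significance level and the result in one sentence: "To capture a pre-post effect of 0.50 with a power of 0.80 and a probability of 0.05, a sample of 27 people is needed". It names the software in the same place: "a sample of 27 people is needed for an intervention (calculated with G * Power 3.1". The arm size of 30 is described as "including a hypothetical dropout rate of 10" percent. The section does not say whether the test is one-sided or two-sided. It calls the effect sizes of earlier studies Cohen's d, says that they generally exceed 0.50, and cites one study at 0.90. It does not say which SD standardises the 0.50.

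The section Data management and statistical analysis plans a three-group ANCOVA on the outcomes with the baseline score as covariate, followed by pairwise post-hoc comparisons. For stability at follow-up, "repeated measures analyses of variance will be performed". No one-sided level appears anywhere in the article.

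**The concern.** Every input needed to check the 27 is given except sidedness, and sidedness decides the answer. A level of 0.05 with no qualifier is normally read as two-sided, and on that reading 27 does not give power 0.80 at a paired effect of 0.50. The F-tests named in the analysis section are also non-directional, so nothing in the plan supports a one-sided 5% level.

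At stake is the accuracy of a power claim that the Discussion counts among the strengths of the study. The dropout allowance is built on the same base of 27.

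**Working it through.** **Inputs.** From the Sample size section: effect 0.50, power 0.80, alpha 0.05, n = 27 per intervention, dropout 10%, 30 per arm. Assumption: 0.50 is dz, the mean change divided by the SD of change, which is the effect size that G*Power's matched-pairs test takes.

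**Formula.** For a one-group paired t-test, power is the probability that a noncentral t variable with df = n − 1 and noncentrality dz × √n exceeds the critical t value at level 0.05 (one-sided) or 0.025 (two-sided). The opposite tail is negligible here.

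**Step 1: reproduce the 27.** At n = 27 the noncentrality is 0.50 × √27 = 2.598. The one-sided critical value on 26 df is 1.706, so power is 0.812. At n = 26 power is 0.798. The smallest n reaching 0.80 is therefore 27, and 27 / 0.9 = 30 gives the stated arm size. Both stated numbers are reproduced.

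**Step 2: the same test, two-sided.** At n = 27 the critical value rises to 2.056.

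| n | One-sided power | Two-sided power |
|---|---|---|
| 26 | 0.798 | 0.688 |
| 27 | 0.812 | 0.706 |
| 30 | 0.848 | 0.754 |
| 33 | 0.878 | 0.795 |
| 34 | 0.887 | 0.808 |

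The two-sided requirement is 34 completers, or 34 / 0.9 = 37.8, rounded up to 38 per arm. The effect detectable two-sided with power 0.80 is dz = 0.56 at n = 27 and 0.53 at n = 30. A repeated-measures F-test with two time points and equivalent inputs (f = 0.25, correlation 0.5) also gives 34.

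**Step 3: sensitivity to the standardiser.** If 0.50 is instead a d in raw-score (baseline) SD units, with equal SDs before and after, then dz = 0.50 / √(2(1 − r)), where r is the pre-post correlation. The article gives no r, so these values are assumptions.

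| Assumed r | dz | Two-sided n for power 0.80 |
|---|---|---|
| 0.3 | 0.42 | 46 |
| 0.5 | 0.50 | 34 |
| 0.6 | 0.56 | 28 |
| 0.61 | 0.566 | 27 (power 0.808) |
| 0.7 | 0.65 | 21 |

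**Step 4: the planned between-group contrast.** For one pairwise ANCOVA contrast with n per arm, two-sided at 5% and without multiplicity adjustment, the noncentrality is d / √(1 − r²) × √(n/2). At d = 0.50:

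| Assumed r | Power at 27 per arm | n per arm for power 0.80 |
|---|---|---|
| 0 | 0.44 | 64 |
| 0.5 | 0.55 | 49 |
| 0.6 | 0.62 | 42 |
| 0.7 | 0.71 | 34 |
| 0.8 | 0.85 | 24 |

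The entries 0.71 and 34 at r = 0.7 agree with Step 2 by coincidence. They answer a different question.

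**The case against.** The strongest case on the other side is that no arithmetic slip has been shown. The number 27 is right for a one-sided test, the second hypothesis is directional, and sidedness is a software setting that a condensed article may leave to the full protocol. Part of this stands: the calculation was very probably run correctly with a one-sided setting. But a directional hypothesis does not make the planned F-tests one-sided. The article also states the power figure in full, so the point concerns a stated figure and not an omitted detail.

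A reader might infer that 27 can come only from a one-sided test. The document does not support that. A raw-SD d of 0.50 with a pre-post correlation of about 0.61 also gives 27 two-sided. That correlation appears nowhere in the article, whereas the one-sided paired test needs no extra input, so it is the likelier source but not the only possible one.

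A reader might also infer that the planned analysis has 71% power, or that 34 per arm would secure it. Neither follows, because both figures belong to a one-group pre-post test. Under the assumptions of Step 4, 34 per arm is enough for the ANCOVA contrast only if the correlation is about 0.7 or higher.

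Finally, practical harm is limited. At the cited effect of 0.90, taken as dz, two-sided paired power at n = 27 is 0.99. The study is labelled preliminary, and the Discussion says that only large effects can be detected. This stands, and it lowers the severity. It does not rescue the claim of 0.80 at 0.50, the value that the calculation uses.

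**Conclusion.** The point holds as a correction to a stated power figure, of moderate severity. With 0.50 read as dz, the stated 0.80 at 27 completers is a one-sided figure (0.812 exactly). The two-sided value is 0.706, about 9 percentage points below the stated 0.80. Equivalently, the effect detectable with power 0.80 is 0.56, not 0.50.

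This rests on two readings that the article leaves open: that 0.50 is dz, and that testing is two-sided at 5%. The second is inferred from the non-directional tests named in the analysis section and from the absence of any declared one-sided test. The result says nothing firm about the power of the between-group comparison, which at 27 per arm and a between-group d of 0.50 runs from about 0.44 to 0.85 for assumed correlations of 0 to 0.8.

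**What to change.** Leave N at 90 and change the Sample size text in three respects:

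1. Restate the power sentence along these lines: with 27 completers, the two-sided 5% power of a one-group pre-post test is 0.71 at dz = 0.50 and 0.80 at dz = 0.56.
2. Say that 0.50 is dz (mean change over SD of change) and not a Cohen's d in baseline SD units.
3. Add that these figures describe change within an arm and are not the power of the between-group ANCOVA contrast, which depends on the pre-post correlation. Give the range of about 0.44 to 0.85 at 27 per arm for d = 0.50 and assumed correlations of 0 to 0.8.

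The restated sentence should not be presented as matching the planned tests. The cost is one rewritten sentence and a short addition, with a lower stated power. Recruitment, arms and analyses do not change.

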### Interventions

Because of the pandemic situation due to COVID-19, we chose to deliver the interventions virtually via a collaborative platform, in order to keep a group format while preserving a safe distance. To our knowledge, the effectiveness of the BP when delivered virtually has been evaluated by only one Swedish study, the results of which have just been published [26]. The virtually delivered BP intervention preserved its preventive effect in relation to symptoms of eating disorders, restraint, body dissatisfaction, and internalisation of the thin ideal, compared to a placebo condition of expressive writing and a waiting list control condition.

The BP offers discussions and exercises to make participants realise the cost of pursuing social ideals valuing thinness. The exercises proposed in the BP intervention produce cognitive dissonance [38], which is a cognitive discomfort due to a contradiction between speech and beliefs. This discomfort motivates the person to change their beliefs. The curriculum includes discussions on techniques of the advertising industry and the unique ideal of beauty promoted worldwide, as well as on the costs of pursuing the thin ideal. The participants are also challenged to try behaviours they avoid because their appearance bothers them. Societal activism actions are also discussed. The content of the sessions are manualised and can be downloaded from the website www.bodyproejctsupport.org/resources/materials (4-session French Translation).

The HW allows participants to make personalised changes in their diet and physical activity gradually each week to aim for a health ideal rather than a thin ideal. The programme targets small changes, which are based on behavioural change techniques. Advice is given to participants on what types of changes to introduce to promote their health and how to implement changes sustainably. Difficulties are discussed in the group with a problem-solving approach. The last session introduces a long-term view of lifestyle change. The Healthy Weight programme is manualised and the 4-session script can be downloaded from the website: https://healthyweightsupport.weebly.com/healthy-weight.html.

The two interventions include four 90 minutes sessions given over a month by two facilitators, the principal investigator (IC) or the co-investigator ([name]), and two research assistants. IC and a research assistant will lead all BP sessions and [name] and the second research assistant will lead all HW sessions. The four facilitators were trained to the BP programme by the person who translated the programme into French. They trained themselves on their own to the use of the HW programme. Before starting the study, a dry run of both programmes will be conducted. The sessions will be held on a collaborative platform in groups of six people and will be recorded. The aim of the recordings is to serve as a means of quality control regarding the way in which the interventions are delivered. The quality control will be carried out internally, on randomly selected portions of sessions. The participants will have signed a consent form for the recording of the sessions. No health or confidential data will be discussed during interventions, which makes it acceptable to record sessions. These records will be destroyed once the quality control has been carried out.

To increase participants’ adherence, reminders will be sent to them via e-mails between sessions.

The waiting list will consist of two assessments, each separated by a one-month interval. Following this waiting time, participants will receive the BP intervention because it is the intervention that has achieved the larger effects [21,22]. A third assessment will take place at the end of the intervention.

### Blinding

The participants or the people performing the interventions will not be blinded to their conditions. In order to minimise bias, the main statistical analyses aimed at evaluating the hypotheses will be performed by a statistician who is blinded to the participants’ allocation.

### Measures

Participants will complete the following questionnaires before the interventions or the waiting list (T0), after the interventions or the waiting list (T1), and after one month of follow-up or intervention (T2).

#### Primary outcome

Body dissatisfaction will be assessed with a short version of the *Body Shape Questionnaire* (BSQ-8C) [34,39], which includes eight items, such as "Have you felt excessively large or rounded?" to be rated on a 6-point Likert scale from 1 *never* to 6 *always*. This instrument has been widely used in research on eating disorders and has been validated in English as well as in French [40].

#### Secondary outcomes

Thin-ideal internalisation will be assessed with the *Socio-Cultural Attitudes Towards Appearance Questionnaire* (SATAQ-4) [41], which includes five items, such as "I want my body to look very thin", to be rated on a 5-point Likert scale from 1 *strongly disagree* to 5 *strongly agree*. This questionnaire has been validated in English and French [42].

Dietary restraint will be assessed with the Restrained Eating subscale of the *Dutch Eating Behaviour Questionnaire* (DEBQ) [43]. This subscale includes 10 questions, such as “Do you intentionally eat foods that are slimming?” to be rated on a scale from 1 *never* to 5 *always*. The DEBQ has been translated and validated in French [44].

Negative affect will be assessed using the *Hospital Anxiety and Depression Scale* (HAD) [45], which is composed of seven items assessing how often the participant experiences anxiety and seven items assessing how often the participant experiences depression on a scale of 0 *never* to 3 *very often*. The HAD has been validated in French [46,47].

Eating disorder psychopathology will be assessed with the *Eating Disorder Examination-Questionnaire* (EDE-Q) [48], which includes 28 items assessing four essential dimensions of eating disorders: dietary restraint, eating concern, shape concern, and weight concern. These four subscales will be used. A total score can also be calculated, which will be used as an indicator of signs of eating disorder psychopathology. Moreover, the monthly frequency of unhealthy behaviours, such as binge eating or inappropriate compensatory behaviours, and height and weight, will be retrieved from this questionnaire as well. Although the participants should not have eating disorders in order to be included in the study, symptoms of eating disorders are present on a continuum, and it is hoped that the interventions lead to improvement. The EDE-Q has undergone validation studies in English and French [49].

Socio-demographic variables will also be included in the questionnaire, in order to collect age, nationality, time spent in Switzerland, university, and faculty.

#### Acceptability

A satisfaction index for the interventions will be added to the post-intervention questionnaires. It includes four questions, “did you find the intervention useful?”, “did the intervention help you?”, “were the key points of the intervention understandable?”, “did you find the exercises useful?” to be rated on a 5-point Likert scale from 1 *not at all* to 5 *very much so*. The satisfaction index will be calculated as a mean of the four subscales. This index and the number of sessions attended by the participants will be used to assess interventions acceptability.

During the last session of the interventions, we will also collect the participants’ comments on the topics that they have appreciated or disliked, and on the topics that might have seemed odd, to allow cultural adaptations if needed, or improvements, to be made to the interventions. We selected the following questions from the focus group discussion guide used by Jarman et al. [50] to prompt the discussion:

Thinking about the programme sessions, what did you like about them? Did any particular activities or moments stood out for you?What did you dislike about the programme sessions? Did any particular activities or moments stood out for you?Did you feel comfortable talking during the sessions? If not, why and how can we overcome this or make you feel more comfortable?What do you think we could do to improve the sessions? Was anything missing?How do you think we should advertise it to other young women?Do you have anything else you would like to say?

The participants’ answers will be transcribed verbatim and analysed with thematic analyses [51].

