## Abstract

Because of the serious consequences of eating disorders on young women’s lives and because of the lack of specialised care facilities, assessing and implementing evidence-based prevention interventions is necessary. Switzerland, like other Western countries, has high prevalence rates of eating disorders. However, no prevention interventions have been evaluated in this country so far. This paper presents the protocol of a preliminary study with the aim to evaluate the acceptability and effectiveness of two interventions, the Body Project (BP) and the Healthy Weight Program (HW), for female students from French-speaking Switzerland. These two interventions were chosen because they have been widely evaluated and they proved to be effective in various countries. They take place in groups and include four weekly sessions over one month. Because of the pandemic situation, the group sessions will take place online on an collaborative platform. The design is a three-arm randomised controlled study. Ninety female students aged 18–25 and presenting with at least moderate body dissatisfaction will be randomised into three groups: (1) one-month BP intervention, (2) one-month HW intervention, and (3) one-month waiting-list control group followed by the BP intervention. Assessments of body dissatisfaction, thin-ideal internalisation, dietary restraint, negative affect, and eating disorder psychopathology will be conducted before and after the interventions or waiting list and after a one-month follow-up. ANCOVA and ANOVA with repeated measures will be used to assess group differences and follow-up stability. Acceptability will be assessed with a questionnaire on participants’ satisfaction with the interventions, group discussion at the end of the intervention, and with participants’ rate of attendance to the group sessions. The study results will provide additional data on these two eating disorders prevention interventions and will suggest ways for their dissemination and further evaluation in Switzerland.

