
The acceptability of the two interventions, assessed by the number of sessions that the participants attend, their satisfaction with the intervention, and qualitative comments provided by the participants, will be good for both interventions;The two interventions BP and HW will improve body dissatisfaction (primary outcome) as well as thin-ideal internalisation, dietary restraint, negative affect, and eating disorder psychopathology (secondary outcomes), compared to a waiting list;The improvements observed in the intervention groups (BP and HW) will be maintained after one month of follow-up.

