## Discussion

This study will provide initial results on the acceptability and effectiveness of the BP and HW interventions in French-speaking Switzerland. These results will be disseminated through scientific articles and at conferences on eating disorders and body image. In order to disseminate the results in the community, we will communicate them to the two main French-speaking websites dedicated to adolescents and young adults health promotion. Potential cultural adaptations that might emerge from the participants’ comments will be considered and discussed with the designers of the interventions, before being adopted. We do not expect major adaptations, since at least the BP programme was used successfully in other cultures than the US without fundamental change [25,26]. In addition, these preliminary data will be used as a basis to write a grant proposal for national funding agencies for investigating the mediating or moderating factors involved in the prevention of eating disorders. In particular, the mechanisms at play in the HW are not yet well understood [53]. An analysis of the stability of the effects of interventions, as well as their effect on the development of eating disorders, requires a larger sample and a longer follow-up period.

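### Qualitative acceptability comments come only from a group discussion in the last session, so leavers' reasons and private criticism have no route in

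*Protocol article*

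**What the plan says.** Hypothesis 1, at the end of the Introduction, is that acceptability "will be good for both interventions". It has three components, being "assessed by the number of sessions that the participants attend, their satisfaction with the intervention, and qualitative comments provided by the participants".

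The Acceptability section gives the route for the third component: "During the last session of the interventions, we will also collect" what participants have to say about the topics they liked and disliked. The Abstract lists the same element as a "group discussion at the end of the intervention, and with participants’ rate of attendance to the group sessions". The answers are to be transcribed and analysed thematically. One of the listed prompts is "Did you feel comfortable talking during the sessions".

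Under Interventions, the sessions are "given over a month by two facilitators, the principal investigator" or the co-investigator, with research assistants. One pair leads every BP session and the other pair every HW session, in groups of six, with recording.

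The other two components work differently. The four-item satisfaction index belongs to the post-intervention questionnaires, which run in REDCap as surveys sent by e-mail (Data management and statistical analysis). Attendance is a count of sessions.

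The Discussion says what the comments are for: "Potential cultural adaptations that might emerge from the participants’ comments will be considered and discussed with the designers of the interventions".

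**The concern.** The route for the comments selects on the thing being studied. Someone who found a programme unhelpful or uncomfortable is more likely to stop coming or skip the last session, and is then not heard. Those who do attend must voice dislikes aloud, before the other group members and, very probably, the people who ran the programme. The prompt about comfort in talking is put to the same group in which any discomfort would have arisen, so those it is aimed at are the least likely to answer it.

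Acceptability is the first hypothesis and the stated sense in which the study is preliminary. The comments are also to inform adaptation. This matters particularly for HW, which the team translates and adapts itself and for which the facilitators were self-trained. If the comments come mainly from those who stayed and are willing to speak, the adaptations will be guided by the participants who needed them least.

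**Working it through.** No sample size or error rate depends on this point, so the check is mainly a comparison of what the document says about each component.

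**Step 1: routes side by side.**

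| Component of hypothesis 1 | Route stated | Needs presence at session 4? | Spoken before the group? | Shows why someone left or what to change? |
|---|---|---|---|---|
| Sessions attended | Count | No | No | No |
| Satisfaction index | E-mailed REDCap survey after the intervention | No | No | No: four rated items on usefulness, help, clarity and exercises |
| Comments | Group discussion in the last session | Yes | Yes | Yes |

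The only component that can explain non-acceptability is also the only one that requires presence and speaking in the group.

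**Step 2: is there another route for comments?** The article describes no exit contact, written field or anonymous channel. The individual debriefing (Ethics) is offered one month after the last assessment for closure and possible referral, and is not said to gather acceptability comments. Withdrawals adds participants who leave under its rules; any who do so before session 4 are also unheard. The limitations listed in the Discussion do not mention the matter.

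**Step 3: who hears the comments?** Interventions assigns one pair to all sessions of a programme, and Acceptability places the discussion inside a session. That the pair moderates it follows by inference; no moderator is named.

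**Step 4: scale, using the plan's only related figure.** Sample size takes 27 per intervention and a hypothetical 10% dropout: 27 / (1 − 0.10) = 30, which reproduces the plan's 30 per arm. If that 10% were also the share absent from session 4 (an assumption, since it was set for the pre-post calculation):

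- per arm: 0.10 × 30 = 3
- BP and HW arms together: 0.10 × 60 = 6
- including waiting-list participants who later receive BP: 0.10 × 90 = 9

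The chance that all six members of a group are present, if absences are independent (also assumed), is (1 − q)^6:

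- q = 0.10: 0.90^6 = 0.53
- q = 0.20: 0.80^6 = 0.26

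Under these assumptions, between about half and about three quarters of groups would hold the discussion with at least one member missing. The size of any social-desirability effect among those present cannot be derived from the document.

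**The case against.** A reader might infer that hypothesis 1 as a whole misses the participants for whom a programme was not acceptable. The document does not support that. Attendance registers directly those who stop coming, and the satisfaction survey can reach them by e-mail and is not answered before peers. This part of the objection stands, and it confines the point to the comments.

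A reader might also infer that the comments must come out favourable whatever the truth. That goes too far. The prompts ask openly what was disliked, what was missing and whether people felt uncomfortable. Bias towards favourable comment is plausible, but its size is unknown. Thematic analysis yields themes, so no percentage of favourable opinion is at stake. Nor does the 10% dropout set a minimum number of silent participants: someone may comment in session 4 and then not return the questionnaire.

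The role of the comments should not be overstated either. Adaptations are to be discussed with the programmes' designers before adoption, and no major ones are expected.

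Finally, the missing level at which acceptability would count as good is a separate matter. A condensed article may leave it to the full protocol or analysis plan, so it is not part of this point.

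What survives is that the collection route is stated, not merely left out, and that neither of the other two components supplies what it loses.

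**Conclusion.** The point holds for the qualitative component of hypothesis 1 only. The comments omit anyone who stopped or missed session 4, and criticism has no private route. The information lost or skewed is the reasons for non-acceptability and the suggestions for adaptation. The fact of leaving and the level of satisfaction are still measured, although people who leave may also fail to return the survey.

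The number affected is unknown. About 3 of 30 per arm is an order of magnitude, resting on the assumption that the plan's dropout allowance also describes absence from session 4. The role of the facilitators as moderators is inferred. The randomised comparisons and the primary outcome are unaffected. This is a worthwhile, inexpensive improvement to the evidence meant to guide adaptation.

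**What to change.** Keep the group discussion as planned and make these additions:

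- Add the same prompts to the post-intervention REDCap questionnaire as open-text items next to the satisfaction index, with one further item asking the reason for missing sessions or stopping.
- Send them to everyone allocated to BP or HW at T1, whatever number of sessions they attended, and to waiting-list participants at T2, after their BP.
- Include the written answers in the thematic analysis.
- Report how many participants contributed comments by each route, so that readers can see whose views are represented.

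The cost is protocol wording and a slightly longer form on a platform already in use. Written answers will be briefer than live discussion, which is a reason to keep both. People who do not return the questionnaire will still be missed, so the change reduces the gap without closing it.
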